### Recruitment and consent of women

We will conduct a census in all households in the study area and record the names and contact details of all consenting women in an electronic system with a unique I.D. number. Our surveillance worker will then conduct door-to-door bi-monthly visits to identify women missing two menstrual periods in a row. All such woman will undergo a pregnancy test with a sensitive pregnancy urine test kit (Excel®). We will invite women to participate who test positive in the study with informed written consent. Based on experience with our previous research with similar design and settings, we expect at least 95% of mothers will consent.

### Randomisation and allocation of treatments

The treatments will be assigned to eligible clusters using a fixed randomisation scheme with a uniform allocation ratio of treatments, stratified by unions. We will use Stata® software to generate the random allocation sequence. Stratification of clusters based on unions will ensure geographic balance across the study area neutralising the effect of contextual factors. It will also mean that both the intervention and control groups will receive similar maternal and child health and nutrition services from the government. The only difference between the treatment arms will be the mobile phone nutrition BCC with cash transfers in the intervention arm. This design will control for potential confounding factors (observed and unobserved) as we will randomly allocate an adequate number of clusters (104 in total) to one of the groups. Contamination of interventions will be constrained by geographic separation of clusters, and by the nature of the interventions (mobile phones and cash). The nature of the intervention precludes the masking of the treatments.

### Evaluation

#### Data collection team

To minimise assessment bias because of a lack of trial blinding, we will separate the intervention and evaluation staff. During the training of the evaluation team, we will not reveal the trial hypotheses or interventions. Each surveillance worker will record the details of married women aged 15–49 years in her village who consent to menstrual monitoring and monthly follow up. She will inform the study health worker if a woman reports two missed periods. The study health worker will then visit, validate the pregnancy through a pregnancy kit and enrol the woman. For surveillance and quantitative data collection, there will be 30 surveillance workers and 15 data collectors who will be supervised by three field supervisors. Also, we will form seven teams with each team consisting of two persons for child anthropometry measurements. There will also be two senior-level field data collectors for the 24-h dietary intake measurements in a sub-sample. At the central level, two senior researchers and three junior researchers will provide overall supervision and management of field activities and data collection.

#### Data collection schedule

Standard questions on infant feeding practices will be collected monthly until 9 months and every 3 months after that until 18 months (Fig. 4). Along with infant feeding practices, we will also record maternal recall of symptoms from the preceding 2 weeks of common childhood illnesses (diarrhoea, acute respiratory illnesses and fever) using standard questions from BDHS [4, 44]. Further, at baseline, we will collect data on social, economic and demographic characteristics along with household food security and maternal nutrition knowledge. We will measure household food security and maternal nutrition knowledge at end-line. Specially trained interviewers will collect 24-h dietary recalls using standard methods from the mothers at baseline, in the third trimester and for the children at 9, 12, & 18 m (Fig. 4). Anthropometry will be collected within 72 h of birth and monthly until six months and then at 9, 12, & 18 m (Fig. 4). Trained research assistants will collect weight and height measurements using established methods [45]. We will conduct these standardisation exercises before and during data collection.

**Fig. 4 Fig4:**
[figure not shown]
Schedule of enrolment, intervention and assessment

#### Electronic data collection tool

The team in the field will use an Android Tablet interactive data collection tool for data capture. The software navigates the data collectors during each specific evaluation interview. Once they complete an interview, the data are uploaded to the server at the International Center for Diarrheal Disease Research, Bangladesh (icddrb) and merged with existing data. A copy of the data remains on the tablet. Tablets are synchronised with the server each day. We will monitor data regularly, to allow real-time adjustments for any data inconsistencies. A team of four, led by a lead researcher, will collect qualitative data. They will record the interviews then transcribe and translate them into English within a week of data collection.

### Statistical analyses

Data analyses will be by intention to treat and by a statistician blinded to the treatment group to reduce interpretation bias. We will conduct the analyses at the mother-infant dyad level and will adjust for cluster randomisation [46]. In primary analyses, we will compare the prevalence of stunting (length-for-age < − 2 Z) in children at 18 months using Pearson’s chi-square tests and 95% confidence intervals for the group difference adjusted for clustering. In secondary analyses, we will examine each outcome variable (birth weight, feeding patterns, and mean nutrient intakes) taking account of the repeated measurements within children by using separate mixed models. We will use linear mixed models for continuous outcomes (e.g. height-for-age Z) and generalised linear mixed models for non-continuous outcomes (e.g. binary outcomes such as exclusive breastfeeding). Models will include treatment group as a fixed effect, infants as a random effect to account for repeated measurements, and community-cluster as a random effect to account for cluster effects. We will use STATA® for all analyses.

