### Cluster recruitment

Each cluster consists of an average of 750 households. Of total 552 villages (451 in Ullahpara and 101 in Khamarkhanda) in our study area, we will include 389 accessible villages to give a total of 166 clusters, of which we will randomly select 104 clusters with an equal number of clusters in each arm of the trial (Fig. 1). The research team will request written approval for the study from the Directorate General of Health Service (DGHS) under the Ministry of Health & Family Welfare before allocating the clusters to the control or trial intervention.

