#### Social, economic and demographic characteristics

Data for social, economic and demographic characteristics will be collected in baseline questionnaires using Demographic and Health Survey methods which include an inventory of household assets to construct a wealth index [41] and the mother’s socio-demographic and reproductive characteristics.

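### Clusters are randomised within unions, but neither the primary chi-square nor the secondary models include union, so the analysis is valid but conservative if unions differ

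*Protocol article*

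**What the plan says.** In the protocol article, the section on randomisation and allocation of treatments assigns clusters "using a fixed randomisation scheme with a uniform allocation ratio of treatments, stratified by unions". It gives the purpose: "Stratification of clusters based on unions will ensure geographic balance across the study area neutralising the effect of contextual factors". The section on cluster recruitment sets the numbers: "we will randomly select 104 clusters with an equal number of clusters in each arm of the trial", so 52 clusters per arm.

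The section on statistical analyses opens with a general rule: "We will conduct the analyses at the mother-infant dyad level and will adjust for cluster randomisation". It then names the primary analysis of stunting at 18 months as Pearson "chi-square tests and 95% confidence intervals for the group difference adjusted for clustering". For the secondary outcomes it lists the model terms: "Models will include treatment group as a fixed effect, infants as a random effect to account for repeated measurements", plus a random effect for the community cluster. Union appears in neither place.

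**The concern.** Stratifying the allocation balances the arms on whatever differs between unions, so that part of the variation cannot contribute to the difference between arms. An analysis that corrects for cluster but not for union still counts it as noise. The estimated standard error then exceeds the true one, the interval is too wide and the test rejects too seldom. The article expects unions to matter, since neutralising contextual factors is its reason for stratifying.

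What is at stake is efficiency, not false-positive control. The secondary models have the same gap: a cluster random effect without union puts the between-union component into the cluster variance.

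**Working it through.** **Inputs.** From the section on sampling frame and sample size: 40.2% v 34.0% stunted, 1092 per arm, 104 clusters (2184/104 = 21 each), two-sided 5%, 80% power, design effect 1.28, and ICC 0.0051 at cluster size 20. Assumed, because the article does not give them: the share s of between-cluster variance lying between unions, and the number of unions (needed only for the simulation and the degrees of freedom).

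**Reproducing the plan's sample size.** The pooled-variance formula for two proportions gives 952 per arm, or 984 with continuity correction.
- ICC 0.0051, m = 21: design effect 1 + 20 × 0.0051 = 1.102. Then 984 × 1.102 = 1084 per arm, and 1084/21 = 51.6 clusters, rounded up to 52. 52 × 21 = 1092, the stated figure.
- Design effect 1.28: 952 × 1.28 = 1219 per arm, which is not the stated figure.
- ICC 0.0051 at m = 20 implies 1 + 19 × 0.0051 = 1.097, not 1.28. The two stated inputs conflict. That is a separate matter, but it means both cases must be carried here. At m = 21, a design effect of 1.28 corresponds to ICC 0.28/20 = 0.014.

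**Effect of omitting union.**
- Design effect without union: DE = 1 + (m − 1) × ICC.
- Design effect with union: DE_u = (1 − ICC) + m × ICC × (1 − s).
- Standard error too wide by the factor r = √(DE/DE_u).
- True two-sided alpha without union = 2 × [1 − Φ(1.96 × r)].
- Power = Φ((d√(1092/DE) − A)/B), with d = 0.062, A = 1.96 × √(2 × 0.371 × 0.629) = 1.339 and B = √(0.402 × 0.598 + 0.340 × 0.660) = 0.682. DE_u replaces DE when union is in the analysis.

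| Case | s | DE_u | SE too wide | True alpha without union | Power without union | Power with union |
|---|---|---|---|---|---|---|
| ICC 0.0051 (DE 1.102) | 0 | 1.102 | 0% | 0.050 | 81.6% | 81.6% |
| | 0.25 | 1.075 | 1.2% | 0.047 | 81.6% | 82.5% |
| | 0.5 | 1.048 | 2.5% | 0.045 | 81.6% | 83.4% |
| | 1 | 0.995 | 5.2% | 0.039 | 81.6% | 85.3% |
| DE 1.28 (ICC 0.014) | 0 | 1.280 | 0% | 0.050 | 75.6% | 75.6% |
| | 0.25 | 1.206 | 3.0% | 0.044 | 75.6% | 78.0% |
| | 0.5 | 1.133 | 6.3% | 0.037 | 75.6% | 80.5% |
| | 1 | 0.986 | 13.9% | 0.026 | 75.6% | 85.6% |

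**These losses are upper figures.** The column without union is the power implied by the plain design effect. Under stratified allocation the unstratified test does slightly better, because its estimate really varies with DE_u although its standard error uses DE: power = Φ((d√1092 − A√DE)/(B√DE_u)). At DE 1.28 and s = 0.5 this is Φ((2.049 − 1.339 × 1.131)/(0.682 × 1.064)) = 76.9%, a gap to 80.5% of 3.6 points rather than 4.9. At ICC 0.0051 and s = 1 it is 82.8%, a gap to 85.3% of 2.5 points rather than 3.7.

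**Simulation.** 4000 trials per setting, 104 clusters of 21, 13 assumed unions, cluster-level t tests without v with union terms:
- ICC 0.0051, over s from 0 to 1: power 81.1 to 82.3% v 81.3 to 84.3%; alpha 0.041 to 0.050 v 0.045 to 0.051.
- ICC 0.014, s = 0: power 74.0% v 74.1%; alpha 0.053 v 0.053.
- ICC 0.014, s = 0.5: power 75.9% v 79.2%; alpha 0.044 v 0.055.
- ICC 0.014, s = 1: power 77.0% v 83.8%; alpha 0.028 v 0.052.

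The direction agrees with the formulas, and the gains are close to the smaller figures. The simulated test is a stand-in for the planned chi-square, not the same procedure.

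**The case against.** The strongest reply is that this is a small efficiency remark. Alpha never rises above 5% by the formulas. At the ICC that reproduces the sample size, planned power stays near 81 to 82%, and the gain is under 2 points unless more than half of the between-cluster variance lies between unions. The share s is assumed throughout. If unions do not differ, nothing is gained. All of this stands, and it limits the point to lost precision.

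It can also be said that a design-based Pearson test can carry stratum identifiers as well as cluster identifiers, and that an analysis plan not shown may add them. That is fair: the article is silent on union and does not rule it out. But it names the primary test and lists the terms of the secondary models, and an analysis plan that followed that text would leave union out.

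Two stronger readings are tempting and should not be made:
- A reader might infer that only the interval is adjusted for clustering, so that the p-value comes from a naive Pearson test with inflated type I error and may conflict with the interval. The preceding sentence in the same section applies the cluster adjustment to the dyad-level analyses generally, and the study design section also says clustering will be accounted for. The phrase on clustering can govern the tests as well as the intervals. The naive test is not the plan.
- A reader might count the absence of baseline covariates, such as the wealth index, as part of the defect. A cluster-corrected comparison without covariates is valid, the article gives no figure for how well any covariate predicts stunting, and the choice of covariates is commonly left to an analysis plan. Adjustment is an option, not a correction.

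**Conclusion.** The point holds as a mismatch between a randomisation stratified by union and an analysis that does not mention union. Inference as written is valid but conservative when unions differ.

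Its importance turns on two unknowns: the share s, and which of the two conflicting clustering inputs is nearer the truth. At ICC 0.0051 the cost is minor. At design effect 1.28 it could decide whether the trial reaches its 80% target: at s = 0.5, power with union is 80.5%, against 75.6% on the plain design effect, or 76.9% allowing for the stratified allocation. The documents support neither a claim of excess false positives nor a claim that the unadjusted comparison is wrong.

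**What to change.** State that the primary analysis includes union as strata. Either a stratified cluster-adjusted test or a cluster-adjusted model with union fixed effects will do, provided that one analysis gives both the p-value and the risk difference with its 95% interval. Add union to the secondary mixed models. Keep the unstratified cluster-adjusted chi-square as a sensitivity analysis. Any covariate adjustment can be decided separately.

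The cost is wording plus one degree of freedom for each union after the first. Of about 102 at cluster level (104 − 2), an assumed 13 unions would leave 102 − 12 = 90 and an assumed 17 would leave 102 − 16 = 86. If unions turn out not to differ, the change in power is negligible (74.0% v 74.1% in the simulation at ICC 0.014).

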### Economic analyses

An economic evaluation will estimate the incremental cost-effectiveness ratio (ICER) from a societal perspective for mobile phone nutrition BCC plus cash transfer intervention compared to usual care. We will conduct the economic assessment in two phases: 1) Trial based evaluation to assess incremental costs and effects of adding this intervention to usual care; 2) Modelled analysis for estimating lifetime costs & disability for mothers and children. Costing templates (Costit) will be followed to record the financial and economic costs of our intervention. We will include all items of the program and household level costs in the tool. For the program cost, we will track all expenses incurred throughout the implementation period. We will distinguish fixed costs and variable costs. The fixed costs will cover the costs of developing the BCC content and mobile application, the costs associated with the cash transfer, the cost of the mobile phone. Variable costs will include the costs for intervention (reaching out to women), the maintenance of mobile phones, monitoring and troubleshooting. At end-line, we will use the program summary costs, which includes costs incurred for program implementation and for care-seeking at an individual level, to calculate the total cost. We will collect the costs of care-seeking during baseline, end-line and follow up visits during the intervention period. We will disaggregate costs of illness into two components – direct costs and indirect costs. Direct costs will include household expenditures related to treatment-seeking (medical expenses, such as physician’s fee, drug costs, cost of hospital stay - both for the patient and accompanied person) along with non-medical expenses such as transport costs. Indirect costs will include information on loss of household productive labour time (monetised loss of working hours) for patients and accompanying household members.

### Data monitoring

#### Electronic data monitoring tool

We will develop an online monitoring system, which will provide real-time information on enrolment status, adherence of the data collectors with the evaluation schedule and quality of data for critical variables. This system will allow the field supervisors to monitor the performance of individual data collectors. All reports will be auto generated from the system and will be available for investigators’ assessments.

#### Field monitoring and standardisation

In the field, our Field Research Assistant will observe the interviews and will take duplicate measurements to calculate intra- and inter-observer Technical Error of Measurement (TEM). We will also conduct standardisation sessions for field staff. In each session, we will ask data collectors to take duplicate measurements (weight, height, MUAC for women; weight, length, head circumference for children) on ten volunteers. We will calculate the intra- and inter-observer Technical Error of Measurement (TEM) and use the results to identify poor data collectors for re-training and additional field support.

#### Data safety and monitoring board

We will form an independent data safety and monitoring board (DSMB). It will assess the interim data, data quality, data completeness, adequacy of compliance with goals for recruitment and retention, and factors that might affect the study outcome or compromise the confidentiality of the trial data. We will notify the DSMB of any unintended effects of the trial intervention.

#### Access to data

All data will be accessible to the study investigators. The investigators will have the right to analyse and publish data. We will only share datasets externally after we have removed all personally identifiable information and with every reasonable effort to keep the identification of study subjects in the strictest confidence.

#### Dissemination plan

The research team will share the lessons learned from the study widely throughout Bangladesh and among global audiences. The authors will organise dissemination seminars to share the findings with the relevant stakeholders. We will present the intermediate and immediate results which support the hypotheses generated from the trial at national and international conferences and publish them in conference proceedings. We will publish the analysis of the outcomes in the form of internal documents, working papers, and in international peer-reviewed journals. We will base authorship eligibility on recommendations of the international committee for medical journals editors (ICMJE).

## Discussion

This study protocol describes a cluster randomised controlled trial of a cash and nutrition education-based intervention, to improve the nutritional status of children less than 2 years of age to reduce stunting. Poor nutritional status of children is a major global public health problem in low- and middle-income countries [47] accounting for 35% of under-5 child deaths and 33% of the disease burden in this age group [47]. It is a significant problem in Bangladesh, which has > 20% low birth weight [5], the second-highest prevalence of child underweight globally [48] and a very high prevalence of stunting [4]. Despite falls in poverty, the levels of extreme poverty, food insecurity and vulnerability remain high with 21 million people living in extreme poverty [3]. Developing effective combinations of nutrition-specific and nutrition-sensitive interventions will be integral components of efforts to develop sustainable development policies and programs for nutrition and to prevent stunting [13]. In recent years, there has been an increasing interest in the use of cash transfer to reduce malnutrition. In a previous study, we found that cash alone is unable to prevent child stunting, and only the combination of cash transfers plus nutrition BCC improved child growth to reduce stunting. However, both cash transfer and face-to-face nutrition counselling are expensive. So, it is of high priority to find a cost-effective delivery platform and to produce strong evidence that the interventions will work best in the Bangladesh country context. Without strong evidence, it would be difficult for policymakers to scale up such an intervention nationwide. The proposed trial will provide high-level evidence of the efficacy and cost-effectiveness of mobile phone nutrition behavior change communication, combined with unconditional cash transfers in reducing child undernutrition in rural Bangladesh. This trial of an innovative approach to enhancing the impact of cash transfers on child nutrition will be a leading study to show an efficacious and cost-effective approach to reducing maternal and child undernutrition in a low-income food insecure population.

## Data Availability

Not applicable.

## Abbreviations

ERC: Ethical Review Committee
HREC: Human Research Ethics Committee
NHMRC: National Health and Medical Research Council
